### 8.13 End of trial

The ethics committee and Sponsor will be notified at the end of the trial or within 15 days if terminated early.

### 8.14 Assessment of engagement at 6-week treatment end

Participants in the IonaFFV arm will be asked to complete the MAUQ at treatment end.

### 9 INTERVENTIONS

### 9.1 Iona mobile phone app adapted for Female veterans (IonaFFV)

The intervention is reported according to the Template for Intervention Description and Replication (TIDieR) Checklist (Hoffman et al., 2014).

**Table 10 TIDieR Checklist**

| Item | Description |
| --- | --- |
| Brief Name | Iona: Female forces veterans (IonaFFV) |
| Why | Help-seeking barriers to mental health services experienced by female veterans result in them being underserved and underrepresented compared to male veterans, male /female servicing personnel or civilians (Leung et al., 2020). When compared to access rates of serving women or male veterans, they are approximately 50% of what would be expected. This is problematic given serving females experience high levels of in-service adversity making increased prevalence of mental health difficulties experienced by female veterans likely. Developing acceptable, scalable, and cost-effective interventions delivered by mobile digital apps targeting female veterans presents a potential solution to improving access. However, efforts to ensure interventions are adapted to meet the preferences and needs of female veterans to enhance acceptability and engagement are first required. Using a focus group methodology and working alongside a female veterans involvement group, an understanding of adaptations needed to enhance acceptability have now been used to adapt the XSW app for female veterans. However, whilst enhancing acceptability, little is known regarding the potential effectiveness of the app in the treatment of depression or Generalised Anxiety Disorder. The need to undertake a feasibility RCT to examine potential effectiveness of the app versus a SHAM control app is therefore needed before considering wider evaluation and potential implementation. |
| What | Mobile phone app for the treatment of MDD informed by the clinical protocols commonly adopted for the treatment of depression or Generalised Anxiety Disorder by face-to-face CBT. During initial engagement with IonaFFV participants will be informed regarding the best CBT technique based on outcome measures taken at baseline. Following participants gaining an understanding of their depression or GAD using a CBT model they are provided with an option of evidence-based CBT techniques for depression. Options include Behavioural Activation, Cognitive Restructuring with Behavioural Experiments and Worry Management (Problem Solving with Worry Time). Support using any of the intervention techniques is provided by AI for the duration of the 6-week treatment period. |
| Who Provided | The intervention is solely provided in-app, there is no human support. |
| How | Participants will be encouraged to use the app to engage with the CBT technique for 6 weeks. Support is provided in-app by an AI driven chatbot, no human support is available. |
| Where | The intervention is provided by the IonaFFV app, employing the CBT techniques with support provided in-app by an AI driven chatbot. |
| When and How Much | Following download of the app, participants will be encouraged to engage with the intervention on their own over the next 6 weeks. It will be emphasised within the app that engaging for a manageable amount of time on a regular basis is better than trying to use the intervention for a long period of time periodically. However, the exact amount of time the participant engages with the intervention will be determined by them. |
| Tailoring | The IonaFFV intervention has been extensively adapted and co-produced for es-servicewomen through focus groups and wider consultation prior to this Feasibility RCT. |
| Modifications | The intervention used within the study is an adaptation of the Iona app for the general population developed by Iona Mind Inc. Modifications to the IonaFFV app for female veterans are largely focussed on language, examples, armed forces related quotes, imagery. |
| How Well | Log-data regarding engagement with the app and specific lessons and features with time engaged will be taken for each participant. Furthermore, the MAUQ will take participant responses regarding general usability. |

###

### 9.2 SHAM control app

Participants randomised into Iona SHAM CONTROL app consisting of approximately the same number of lessons as Iona FV, with repeatable “meditation-like” exercises. The “meditation-like” lessons will consist of text, video and audio, similar to that of the IonaFFV app, and the exercises will again be text, video and audio, with the length of each lesson and exercise adapted to be approximately the same as the average engagement time per session with IonaFFV in order to match time on task for the user. Iona SHAM CONTROL will be delivered within the same app framework using approximately the same app and cloud infrastructure as IonaFFV to ensure a consistent look and feel and user experience across both apps. Similar to IonaFFV, notifications and emails will encourage the user to engage daily with the techniques with the aim of achieving a similar usage pattern between both apps. Iona SHAM CONTROL also contains modules on therapies that while commonly recognized are not evidence-based, such as Dream Analysis, again delivered using text, images and audio in a similar manner to IonaFFV. Such modules will be accompanied with related tooling such as a dream diary, presented similarly to the activity diary in IonaFFV, again with the aim of matching time on task and approximate user-experience to IonaFFV without containing any active evidence-based treatment.

### 10 OUTCOME MEASURES/ENDPOINT

### 10.1 Demographic Data

Demographic data will be taken at baseline and address:

- Age
- Gender identity (M/F/neither/both)
- Sexual orientation
- Race/ethnicity
- Service
- Length of service
- Time left armed forces
- Rank leaving service
- Early Service Leaver
  - Optional free response box available to provide reason

### 10.2 Outcome measures

**Table 11 Outcome measures**

| **Measure** | **Description** | **Reliability and Validity** |
| --- | --- | --- |
| **Primary/Feasibility/Methodological Outcomes** | | |
| **Feasibility** | To collect data on number of participants consented, recruited, completed screening, and to assess recruitment method, measure completion (baseline, 6 weeks, 10 weeks), drop out, drop out reason | NA |
| **Secondary Outcomes** | | |
| **Patient Health Questionnaire-9** (**PHQ-9**; Kroenke et al., 2001) | 9-item participant rated questionnaire assessing frequency of symptoms of depression over the last 2 weeks. 4-point scale for each item, with anchors at 0=not at all, 1 = several days, 2= more than half the days, 3 = nearly every day. Unidimensional scale. Available in English, Spanish, German, and Dutch versions. | Leading measure of depression widely used in clinical trials, clinical practice, and as part of the NHS Quality and Outcomes Framework (QOF) for UK primary care and Improving Access to Psychological Treatments (IAPT) Minimum Data Set (MDS). Cronbach’s α =0.89 in primary care, test-retest reliability (ICC) 0.84 after 48 hours. Validation studies indicate positive correlations with measures of functional status (r=0.73), disability days (r=0.39), and symptom-related difficulty (r=0.55) At cut-off of ≥ 10, excellent specificity (0.88) and sensitivity (0.88) with diagnoses of major depression by structured interview, replicated in a UK population (sensitivity 0.80; specificity 0.92). |
| **Generalised Anxiety Disorder-7 (GAD-7**; Spitzer et al., 2006) | 7-item participant rated questionnaire assesses frequency of symptoms of anxiety over the last 2 weeks. 4-point scale for each item, with anchors at 0=not at all, 1 = several days, 2= more than half the days, 3 =nearly every day. Unidimensional scale. Available in English, Spanish, German, and Dutch versions. | Leading measure of anxiety widely used in clinical trials, clinical practice, and as part of the UK NHS IAPT MDS. Cronbach’s α =0.92, test-retest reliability ICC = 0.83. Convergent validity good, r =.72 with Beck Anxiety Inventory, r = 0.74 with Symptom Checklist-90 anxiety scale. |
| **Work and Social Adjustment Scale (WSAS**; Mundt et al., 2002) | 5-item participant rated questionnaire assesses impaired functioning, rated from 0 not at all impaired to 8 severely impaired, with respect to work/education, home management, social leisure, private leisure, and close relationships. Unidimensional scale. | Leading measure of functioning, widely used in clinical practice, and as part of the UK NHS IAPT MDS. Cronbach’s α range from 0.70 to 0.92, test-retest reliability ICC = 0.73. Interactive voice response administration correlated 0.81 to 0.86 with clinician interviews. |
| **Acceptability** | | |
| **mHealth App Usability Questionnaire (MAUQ**; Zhou et al., 2019). | 21-item participant rated questionnaire measured on a 7-point scale ranging from strongly disagree (1) to strongly agree (7). The questionnaire measures acceptability and usability for interactive mental health apps. Three domains explore Ease of Use and Satisfaction, Usefulness and System Information Arrangement. Unidimensional scale. Given IonaFFVis not intended to support communication with healthcare providers from within the app, 5 questions were removed resulting in a 15 item measure. This has been undertaken in other research focused on an Armed Forces community (Parkes et al., 2023), where the app did not support communication with other health care providers. | Commonly adopted measure to rate mobile phone apps across several dimensions. Scale has good internal consistency with Cronbach alpha values of 0.895, 0.900 and 0.829 respectively. |

### 10.3 Timeframe for administration of demographic and outcome measures

**Table 12 Outcome measures timeframe**

|  | **Time Period** | | |
| --- | --- | --- | --- |
| **Outcome Measure** | **Baseline (second screening)** | **6 Weeks Post Treatment Start (Treatment End)** | **10 Week Post Treatment Start (Study End Point)** |
| **Demographic** | **X** |  |  |
| **Primary Outcome (Either Dependent on Second screening/Baseline Severity - Other Secondary)** | | | |
| **PHQ-9** | **X** | **X** | **X** |
| **GAD-7** | **X** | **X** | **X** |
| **Secondary Outcomes** | | | |
| **WSAS** | **X** | **X** | **X** |
| **MAUQ** |  |  | **X** |
| **Feasibility Outcomes** |  |  | **X** |

### 10.4 Primary endpoint/outcome

The primary endpoint of the trial is at 6 weeks post treatment start (treatment end).

### 10.5 Secondary endpoints

The secondary endpoint is at 10 weeks post baseline (4 weeks post treatment end follow-up).

### 10.6 Exploratory endpoints

There are no exploratory endpoints.

### 10.7 Feasibility outcomes

**Table 10 Feasibility Outcomes**

| **Study Recruitment** | | | |
| --- | --- | --- | --- |
| Number of people accessed study web site |  | | |
| Number of people complete screening questions |  | | |
| Number of people screened out | If Yes - Reason | Report by demographics | |
| Number of people consented |  | Report by demographics | |
| **Randomisation** | | | |
| Number of people randomised |  | Report by demographics | |
| Participant blinding randomisation maintained | Yes | | No |
| **Outcome Completion Both Study Arms** | | | |
| Number completed baseline outcome measure | Data completion of each item for each outcome measure | | |
| Number completed end of treatment outcome measures (6 weeks post baseline) | Data completion of each item for each outcome measure | | |
| Number completed final outcome measures 10-week post baseline | Data completion of each item for each outcome measure | | |
| **Recruitment Method** | | | |
| Recruitment method adopted | Number recruited | | |

### 11. STATISTICS AND DATA ANALYSIS

Statistics will be undertaken by the Lead Researcher.

### 11.1 Sample size calculation

As a feasibility RCT there is no sample size calculation. Rather, data will be used to inform a sample size calculation for any subsequent definitive RCT if the data demonstrates potential effectiveness.

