Developing acceptable, scalable and cost-effective interventions delivered by mobile digital apps represents a solution, with good levels of acceptability for female veterans (MeTVeT study; Parkes et al., 2022) justify this proposal to co-develop an app targeting female veterans. Utilising apps to treat mental health difficulties is novel, innovative and can limit stigma, concerns regarding confidentiality or future employment prospects and consistent with female veterans’ self-management preferences (Farrand et al., 2019). When examining the development of apps to support delivery of mental health interventions however, consideration is still required to the evidence-base. Currently, the National Institute for Health and Care Excellence (NICE) restricts recommendations to CBT self-help interventions only when supported by a psychological practitioner for depression (NG222; 2022) and generalised anxiety (CG113; 2020). However, the NHS has begun to successfully implement digital interventions for common conditions such as insomnia via the Sleepio app (Luik et al., 2016) with support provided by AI and is considering increased service provision through non-statutory organisations.

Working with a group of female veterans and others with relevant expertise, this proposal has adapted Ione XSW for this specific group. Following adaptation, the aim of this proposal is to undertake a Phase II Feasibility RCT to explore potential effectiveness, engagement and wider methodological factors of IonaFFV compared to a SHAM control app (Iona SHAM CONTROL). If data suggests IonaFFV has potential to be effective and is acceptable, the study may be used to inform a subsequent Phase III Definitive RCT to treat depression in female veterans. If the app demonstrates acceptability, is engaging and shows promise to be effective, it offers a scalable way to overcome treatment barriers for all female veterans that have currently been underserved.

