### 3 STUDY OBJECTIVE

**Principal objective:** The principal research objective of the Phase II feasibility RCT is to understand methodological uncertainties (e.g., recruitment) associated with running a definitive RCT and to understand intervention acceptability and engagement.

**Secondary objective**: The secondary research objective of the Phase II feasibility RCT is to understand whether there is a potential for the adapted Iona app for female veterans to be effective for the treatment of depression and anxiety.

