### 5 STUDY SUMMARY

| **Title** | Feasibility evaluation of a smartphone based Cognitive Behavioural Therapy (CBT) intervention for the treatment of low mood or support for worry management in female armed forces veterans in England, Wales, and Scotland. | |
| --- | --- | --- |
| **Internal ref. no. (or short title)** | Iona female veterans | |
| **Clinical Phase** | II | |
| **Trial Design** | Feasibility RCT with acceptability and usability questionnaire  Parallel group design with randomisation conducted using block randomisation (blocks of 3) and the trial is conducted with an exploratory framework. | |
| **Trial Participants** | Female forces veterans | |
| **Planned Sample Size** | 60 (30 participants per group) | |
| **Treatment duration** | 6 weeks | |
| **Follow up duration** | End of 6-week intervention engagement period and 4 week follow up (10 weeks post randomisation) | |
| **Planned Trial Period** | 10 weeks post-randomisation | |
|  | **RCTs & measures** | **Outcome domains** |
| **Primary/Feasibility/Methodological Outcomes** | Consented, recruited, completed screening, recruitment method, measure completion (baseline, 6 weeks, 10 weeks), drop out, drop out reason | Feasibility |
| **Secondary Outcomes** | PHQ-9/GAD7  Work and Social Adjustment Scale (WSAS) | Depression/Anxiety dependent on lower score on outcome measure at baseline determining severity.  Functioning |
| **Acceptability** | Mobile Acceptability and Usability Questionnaire (MAUQ) | Acceptability and Usability |
| **Intervention** | Intervention: IonaFFV for depression engaged with for 6 weeks intervention engagement period  Control: Iona SHAM CONTROL app developed to match engagement time | |
| **Route of Administration** | Iona app (IonaFFV) for the treatment of depression or Generalised Anxiety Disorder | |

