### 11.2 Planned recruitment rate

Recruitment of 60 participants into the study will take place online over 16 weeks within a single study site (UNIEXE). Recruitment rate within this timeframe represents a feasibility outcome.

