### 11.5 Primary analysis

Primary analyses will be conducted on methodological and feasibility data, such as recruitment rate and source, completion of baseline measures, study attrition etc. For outcomes related to study feasibility (see Table 10).

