### 11.7 Outcome reporting

Continuous outcomes will be reported descriptively (mean and standard deviation (SD). To explore potential effect sizes and confidence intervals, inferential comparisons will be reported between the two conditions (1) IonaFFV; (2) Iona SHAM CONTROL (control).

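### Onward use of the trial is tied to a secondary effectiveness signal, and the primary feasibility outcomes are not named in the condition

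*Protocol*

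**What the plan says.** The protocol puts feasibility first. Section 3 states: "The principal research objective of the Phase II feasibility RCT is to understand methodological uncertainties", and joins acceptability and engagement to that objective; effectiveness is the secondary objective. Section 5 and Table 11 class consent, recruitment, measure completion and drop-out as primary, and PHQ-9, GAD-7 and WSAS as secondary. Section 11.5 follows suit: "Primary analyses will be conducted on methodological and feasibility data, such as recruitment rate and source, completion of baseline measures, study attrition". Section 11.2 plans 60 women in 16 weeks and adds: "Recruitment rate within this timeframe represents a feasibility outcome".

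Only two places say when the results would feed a definitive trial:

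- Section 11.1: "As a feasibility RCT there is no sample size calculation"; instead, "data will be used to inform a sample size calculation for any subsequent definitive RCT if the data demonstrates potential effectiveness".
- Section 1: "If data suggests IonaFFV has potential to be effective and is acceptable, the study may be used to inform a subsequent Phase III Definitive RCT". The sentence after it also mentions engagement.

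The symptom comparison behind both conditions is described in section 11.7: "To explore potential effect sizes and confidence intervals, inferential comparisons will be reported between the two conditions". The planned size in section 5 is "60 (30 participants per group").

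**The concern.** The outcomes that the trial exists to measure do not appear in the condition for using it, while a secondary contrast that the trial was not sized for does. If the condition steered the decision, a chance difference in PHQ-9 or GAD-7 could weigh more than whether the women could be recruited and followed up.

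Section 11.1 has a second problem. It makes use of the data for sample-size work conditional on a favourable result. The outcome SD, the correlation between baseline and follow-up, and the attrition rate are needed to plan the next trial whichever way the observed difference points.

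**Working it through.** The protocol gives no effect size, SD, power or attrition figure, so it has no calculation of its own to reproduce. The check asks how the symptom contrast behaves as a condition at the planned size.

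**Inputs**
- 30 women per arm, from section 5.
- Assumed: 20 completers per arm as a second case (one third lost). Section 11.3 rules out imputation, so completers are what would be compared.
- Assumed: true effects of 0, 0.3, 0.5 and 0.8 SD; unadjusted comparison; two-sided 5% level where a test is used.

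**Standard error of the difference, in SD units:** SE = √(2/n).
- n = 30: √(2/30) = 0.258
- n = 20: √(2/20) = 0.316

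**Chance of a favourable estimate from an inert app:** the estimate is centred on zero, so 50% at either size.

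**Chance that a real effect d points the wrong way:** Φ(−d/SE). For d = 0.3:
- n = 30: Φ(−0.3/0.258) = Φ(−1.16) = 12%
- n = 20: Φ(−0.3/0.316) = Φ(−0.95) = 17%

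**Power of a t test:** noncentral t with 2n − 2 degrees of freedom and noncentrality d/SE.

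| True effect | Noncentrality, 30 / 20 per arm | Power, 30 / 20 per arm |
|---|---|---|
| 0.3 SD | 1.16 / 0.95 | 21% / 15% |
| 0.5 SD | 1.94 / 1.58 | 48% / 34% |
| 0.8 SD | 3.10 / 2.53 | 86% / 69% |

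Adjusting for baseline helps only in part. With an assumed correlation of 0.5 and 30 per arm, power (normal approximation) rises to 27% at 0.3 SD and 61% at 0.5 SD.

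**A middle reading.** Suppose the condition means an estimate above 0.25 SD. It is met with probability 1 − Φ((0.25 − d)/SE).
- No effect: 1 − Φ(0.25/0.258) = 17% at 30 per arm; 1 − Φ(0.25/0.316) = 21% at 20.
- True 0.5 SD: 1 − Φ(−0.25/0.258) = 83% at 30; 79% at 20.

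So some readings do separate no effect from a moderate one, with error rates of roughly one in five or six each way.

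**What the same 60 women say about feasibility.** Rates among all randomised can be estimated with usable precision. As an example, completion in 48 of 60 (80%) has a 95% Wilson interval of 68% to 88%. The planned recruitment works out at 60/16 = 3.75 women per week, so the recruitment outcome already has a target to be judged against.

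**The case against.** The case on the other side has real weight.

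- **The wording is loose.** Section 1 is background and says only that the study may be used. Section 11.1 concerns when data feed a calculation. Neither says that a definitive trial follows if the condition is met or is abandoned if it is not. This stands. A reader might infer that a trial with poor recruitment and heavy loss would be bound to proceed on a chance difference; the documents contain no such binding rule.
- **Part of the principal objective is covered.** Acceptability and engagement belong to it, and section 1 names both. This stands too. What is left out is recruitment, completion and drop-out. Section 11.3 does use patterns of missingness to inform future design without any effectiveness condition, but that is not a basis for deciding on onward use.
- **The SAP may define potential effectiveness.** It may, so the missing cut-off is not the complaint. The condition itself is fixed in the protocol, and a cut-off would leave it resting on the symptom contrast.
- **The contrast is not worthless.** A reader might infer that 60 women cannot tell an inert app from a useful one. That is too strong: a 0.8-SD effect has 86% power at 30 per arm, and a 0.25-SD bar discriminates moderately well.
- **Feasibility thresholds also err.** An illustrative rule of at least 45 of 60 completing is met 1% of the time at 60% true completion and 99% at 85%, but 24% at 70% and 57% at 75%. No particular level follows from the documents.
- **Overestimation is not shown.** A reader might infer that the next trial would be undersized because a favourable estimate is carried forward. Section 11.1 does not say that the observed effect becomes the target difference.

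One inconsistency bears on this: Table 12 heads PHQ-9 and GAD-7 as the primary outcome. Section 5, Table 11 and section 11.5 say otherwise, as do the research question and objectives, so feasibility is taken as primary here.

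**Conclusion.** The point holds in a limited form. The two stated conditions for informing a definitive RCT hinge on a secondary between-arm contrast, with acceptability and engagement added in section 1, and omit the outcomes that the protocol makes primary. For small to moderate effects that contrast is an unreliable condition: 50% favourable by chance alone, power of 15% to 48% across 0.3 to 0.5 SD and 20 to 30 completers per arm, and the wrong sign 12% to 17% of the time at 0.3 SD. These figures rest on assumed effects and attrition and an unadjusted analysis.

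The absence of a power calculation is acceptable in a feasibility trial and is not criticised. The defect is a badly chosen condition in the protocol's own text. It is a cheap improvement, and it does not invalidate the design.

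**What to change.** - **Section 11.1:** delete the effectiveness condition. State that the SD (with its uncertainty), the baseline-to-follow-up correlation and the attrition rate will inform the definitive sample size whatever the observed effect, and that the target difference will not be taken from this trial's estimate.
- **Sections 1 and 11.1:** base onward use on the primary feasibility outcomes, namely women randomised in 16 weeks against the planned 60, and week-6 and week-10 completion among all randomised, together with acceptability and engagement. The sponsor sets the levels before data are seen.
- **Section 11.7:** state that the between-arm PHQ-9/GAD-7 estimate and confidence interval are descriptive only.

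The cost is a few sentences, with no extra participants, data or procedures. The downside is that the sponsor commits to levels in advance and cannot cite a favourable estimate as the reason to proceed.
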